### Participant randomization and group allocation

Prior to group randomization, a researcher blinded to the future group allocation will classify participants into quartiles based on their peak VO_2_ values. Subsequently, participants from each quartile will be randomly assigned with a 1:1 allocation ratio to 1) supervised group: canoeing and physical activity recommendations (*n* = 18), or 2) unsupervised group: physical activity recommendations (*n* = 18). Following randomization, participants in both groups will be invited to a meeting at the School of Physical Education and Sport at the University of Sao Paulo, where the researcher and the physician will communicate the importance of an active lifestyle and the benefits of physical activity for people living with cancer. In addition, participants will be introduced to the physical activity recommendations booklet (based on WHO guidelines) produced by ICESP. The researcher and physician will outline the goal of achieving physical activity guidelines (i.e., 150 min of moderate-to-vigorous physical activity/exercise per week). Participants will be advised that recommendations can be achieved through separate bouts of activity, such as 50 min per day on three non-consecutive days each week, or 30 min 5 days a week. Following, the physician, who will be blinded to the allocation, will leave the room and the researcher will inform each participant which intervention group they have been allocated to. For participants in the supervised group (canoeing and physical activity recommendations), canoeing training schedules are explained, whereas for those participants allocated in the unsupervised group, best days and times for telephone calls will be arranged so the researcher can remotely investigate whether this group is reaching physical activity recommendations.

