### Assessments

The experimental procedures described below will be performed at baseline (Pre) and after 16 weeks of the intervention (Post), keeping an interval of 3 or 4 days after the last canoeing training session. An exception will be the evaluation of physical activity engagement (time, frequency, and intensity), which will also be monitored at 8 weeks (mid-way point of the intervention). The assessment protocol will be divided into two visits and all procedures will take place at the School of Physical Education and Sport of the University of Sao Paulo (Fig. 3). Participants will be advised to avoid performing physical activities and alcohol ingestion in the 24 h prior to the visits, to refrain from tobacco use and stimulant beverages (coffee, tea) for at least 6 h, and to take their medication as recommended by their physicians. In the first visit, the participants will arrive at 7 am, following an 8-h fasting period and undertake the procedures in the following order: 1) blood sampling; 2) anthropometry and lymphedema measurement; 3) eat a snack consisting of an apple, 150 g of salted crackers, and 200 ml of juice; and 4) cardiorespiratory fitness test. The second visit will take place at least 2 days later to allow the participant to fully recover from the fitness test. For the second visit, the participants will arrive at 7 am and undertake the following evaluation: 1) questionnaires assessing quality of life in cancer survivors, health status, fatigue, body image, and physical activity motivation; and 2) physical functioning tests.

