#### Physical functioning tests

Participants will undertake a circuit of six functional fitness tests, designed to systematically address parameters associated with independent functioning: aerobic endurance, upper and lower body strength and flexibility, and agility/dynamic balance.
i.*Aerobic endurance*: Two-minute step test will be used to assess gait functionality. This test correlates highly with peak oxygen consumption, the primary outcome of this study [92].ii.*Upper body muscular strength*: (i) Maximal isometric handgrip test (Jamar®) will evaluate hand muscle strength during the handgrip test, three alternating attempts will be made for each arm and the highest score will be used for analysis [62]; (ii) Arm curl test will be used to assess arm muscle strength. Participants will do forearm flexions during 30 s with a 2-kg weight. Three alternating attempts will be made for each arm, the first attempt will be considered a familiarization, and the mean of the last two curls will be used for analysis [92].iii.*Lower body muscular strength*: Chair stand test will be used to determine lower limb strength. This test comprises sitting and standing repeatedly without the aid of the arms, for 30 s. Participants will attempt the test once and their score will be used for analysis [62].iv.*Upper body flexibility*: Back scratch test will be used to measure general shoulder range of motion (flexion and extension) in the standing position. Three alternating attempts will be made for each arm. The first attempt will be considered a familiarization and the average of the last two attempts will be used for analysis [92].v.*Lower body flexibility*: Sit and reach lumbar flexibility test will evaluate lower body range of motion using sit and reach bench. Three attempts will be executed. The first attempt will be considered a familiarization and the average of the last two attempts will be used for analysis [93].vi.*Agility/dynamic balance*: Timed up-and-go test will be used to assess functional mobility as the time needed for the participant to get up from a chair, walk 3 m, and return to the original position—Two attempts will be made and the shortest time between them will be used for analysis [94].

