#### Data analysis

The data analyst will receive the raw data coded for participant names and group allocation after completion of data collection. Group allocation will be unblinded after termination of data analyses. The Shapiro–Wilk and Levene’s tests will be used to determine normality and variance equality, respectively, and non-normal scale data will be log transformed. If the transformation does not produce a normal distribution, residual analyses will be performed to test if influential points change the interpretation of the results. If interpretations change, these points will be manually removed. Linear mixed models having group and time as fixed factors and participants as a random factor will be performed for each dependent variable [maximal aerobic capacity (VO_2_ max), daily physical activity, and adherence to physical activity guidelines (assessed via accelerometry and questionnaire), physical functioning (assessed via muscle strength, balance, and agility), self-reported quality of life, fatigue and perceptions of self-image (assessed via specific validated questionnaires), presence of lymphedema, and body composition and immune function]. Baseline differences in outcomes will be examined by independent *t*-test. An analysis of covariance (ANCOVA) will be implemented including the baseline variable as a covariate, group as a fixed factor, and participants as a random factor, in case of differences in baseline values between groups. An intention-to-treat analysis will also be performed in case of a high incidence of missing values, using linear mixed models; the first analysis will be performed removing the missing values, while the second analysis will be performed incorporating the missing data points to determine the impact of missing values in the overall results [96]. Whenever a significant F-value is obtained, a post hoc test with Tukey’s adjustment will be performed. Ordinal data will also be analyzed using mixed models having group and time as fixed factors, and participants as random factor. Nominal data will be compared using chi-square distributions and significance will be determined by residual analyses (< − 2 or > 2).

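### Randomisation is stratified on baseline peak VO2 but no secondary-outcome model uses it: between-woman comparisons lose precision if the outcome tracks fitness, pre-post change contrasts do not

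*Protocol article*

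**What the plan says.** **Design.** Under Participant randomization and group allocation, a researcher blinded to allocation will "classify participants into quartiles based on their peak VO_2_ values". After that, "participants from each quartile will be randomly assigned with a 1:1 allocation ratio to" the two groups of 18. Baseline peak VO2 is therefore on file for every randomised woman.

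**Analysis.** Under Data analysis: "Linear mixed models having group and time as fixed factors and participants as a random factor will be performed for each dependent variable". The list that follows covers the primary and all secondary outcomes. One covariate is mentioned: "An analysis of covariance (ANCOVA) will be implemented including the baseline variable as a covariate, group as a fixed factor", and only "in case of differences in baseline values between groups". That sentence follows the t-tests of baseline differences in outcomes, so the covariate reads as each outcome's own baseline. No group-by-time term is named, and neither the quartile nor peak VO2 appears as a term.

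**Timing.** Under Assessments, the procedures "will be performed at baseline (Pre) and after 16 weeks of the intervention (Post"), so most secondary outcomes have their own baseline. Accelerometry also has a pre-intervention week (Physical activity level). The two-weekly physical activity questionnaire is described only during the 16 weeks (Study design; Assessing physical activity every 2 weeks).

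**Link with fitness.** For the two-minute step test, Physical functioning tests states: "This test correlates highly with peak oxygen consumption, the primary outcome of this study". It gives no figure, and no other secondary outcome is linked to peak VO2.

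**The concern.** Balancing the arms within fitness quartiles removes between-quartile variation from the difference between arms. A model without the quartile or VO2 still counts that variation as error. The estimate is as precise as the design made it, but its reported standard error is too large and its test rejects too seldom.

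For the primary outcome, its own baseline is the stratifying variable, so the ANCOVA at least contains it when it is used. For a secondary outcome nothing planned does. Adherence and activity are central to the trial's hypothesis, and with 36 women any avoidable loss of precision matters.

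**Working it through.** **1. Inputs.** From the article: 1:1 allocation within peak-VO2 quartiles, 18 per group, alpha 0.05, and a pre-post correlation of 0.50 (Power calculation and sample size; given there for VO2 and borrowed here for secondary outcomes). Assumed: the correlation r of a secondary outcome with baseline VO2, the same before and after treatment, over 0.3 to 0.6, with 0.7 as a sensitivity value; roughly normal VO2; quartiles formed once over all 36 women. Outcomes are in SD units.

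**2. The plan's own figures.** 15 × 1.20 = 18 per group, and 2 × 18 = 36. The effect size behind 15 is not stated, so 15 cannot be reproduced. No figure concerns secondary outcomes.

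**3. Outcome without its own baseline.** In a standard normal variable the four quartile means are ±1.271 and ±0.325, so quartile membership carries (1.271² + 0.325²)/2 = 0.861 of the variance. The design removes 0.861r² from the arm comparison while the unadjusted model keeps it:

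reported SE / true SD ≈ 1/√(1 − 0.861r²)

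Continuous VO2 in the model multiplies the SE by about √(1 − r²). Separate simulation runs of 36-woman trials agree:

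| r | SE ratio, formula | SE ratio, simulated | True size of 5% test, no VO2 term | SE cut by VO2, formula |
|---|---|---|---|---|
| 0.3 | 1.04 | 1.04–1.05 | 3.8–4.4% | 5% |
| 0.5 | 1.13 | 1.10–1.13 | 2.8–3.4% | 13% |
| 0.6 | 1.20 | 1.21 | 2.2–2.3% | 20% |
| 0.7 | 1.32 | 1.30 | 1.4% | 29% |

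Adding VO2 restores the size to about 5%. Most of the cut is the reported SE coming down to the truth: at r = 0.5 it falls from 0.331 to 0.287 (−13%), while the true SD of the estimate moves only from 0.294 to 0.287. For an assumed 0.8 SD difference, power rises from 64% to 67%, 65% to 76% and 67% to 83% at r = 0.3, 0.5 and 0.6.

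**4. ANCOVA on the outcome's own baseline.** Residual variance given the baseline is 1 − 0.5² = 0.75. With VO2 added it is 1 − 0.25/(1 − r²).

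- r = 0.3: √(0.725/0.75) = 0.983, a cut of 2% (simulated 1%).
- r = 0.5: √(0.667/0.75) = 0.943, a cut of 6% (simulated 5%).
- r = 0.6: √(0.609/0.75) = 0.901, a cut of 10% (simulated 10%).

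**5. Group effect in an additive group-plus-time model.** A woman's mean of two values has variance (1 + 0.5)/2 = 0.75. At r = 0.5 the quartile explains 0.861 × 0.25 = 0.215 of it, and √((0.75 − 0.215)/0.75) = 0.845, a cut of about 16%. Mixed models fitted to simulated data at r = 0.5 gave 0.298 falling to 0.250, also 16%.

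**6. Pre-post group-by-time contrast.** The covariance of change with VO2 is r − r = 0, so there is nothing to remove. Simulated reported SE over true SD at 36 women is 0.98 to 0.99 for r from 0.3 to 0.7. A quartile main effect in the mixed model left the SE at 0.3292. A VO2-by-time term helps only if baseline fitness predicts change.

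**7. Cost if VO2 is unrelated (r = 0).** With continuous VO2 added to the own-baseline ANCOVA, the half-width of the 95% interval goes from 0.5907 to 0.5936, or +0.5%.

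**The case against.** The strongest reply is that this is a pre-post trial sized with a repeated-measures F test, so the natural arm contrast is group-by-time, where the participant effect already absorbs stable fitness differences. That stands. Physical functioning, fatigue and accelerometry all have baselines. So does the step test, the one outcome the article ties to VO2. A reader might infer that error bars are too wide for every fitness-related outcome; step 6 shows that this is not so for change contrasts. The largest losses are confined to the two-weekly questionnaire and other between-woman comparisons, and no section links questionnaire adherence to fitness.

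The correlations are also assumed, and so is a single set of quartiles over all 36 women. Recruitment over several years could mean quartiles formed in batches, with different balance. Both points stand as limits on the size of the loss.

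It can be said, too, that covariates belong in a fuller analysis plan, which is not shown. If such a plan already contains baseline VO2, nothing needs changing. But the article does not defer the matter: it names the model terms for each dependent variable and its single conditional covariate.

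Finally, a 16% gain in an additive model may say more about the missing interaction than about stratification. That is fair: the gain counts only if that group effect is the intended contrast, which the section does not say.

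**Conclusion.** The mismatch is real: the stratifying variable enters no secondary-outcome model. Its consequence depends on the contrast.

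- **Between-woman comparisons without an own baseline:** at assumed r of 0.3 to 0.6, true size is about 4% down to 2% for a nominal 5% test, and VO2 would cut the reported SE by about 5% to 20%. The additive-model group effect suffers in the same way (16% at r = 0.5).
- **Own-baseline ANCOVA:** a further cut of about 1% to 10%.
- **Pre-post group-by-time:** the standard errors are already correct.

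A reader might also infer bias or excess false positives. Neither follows: omitting the stratifier leaves the comparison unbiased and makes the affected tests conservative. The documents give no correlation of any secondary outcome with VO2, so the size is a range that shrinks to nothing at r = 0. This is a worthwhile, inexpensive gain in precision, not a threat to validity.

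**What to change.** In Data analysis, prespecify continuous baseline peak VO2 as a fixed covariate in the between-arm models of secondary outcomes, in two places:

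- the two-weekly questionnaire outcomes (activity and adherence);
- the post-intervention comparisons that adjust for the outcome's own baseline, with VO2 alongside that baseline.

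The continuous value is preferable to the quartile: it takes 1 degree of freedom instead of 3, and at r = 0.5 without an own baseline it narrows the interval by 13% instead of 11%. No gain should be claimed for change-type or group-by-time contrasts.

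The cost is one model term on a value already measured before randomisation, and under 1% in interval width where VO2 is unrelated to the outcome. The term should be fixed before group codes are opened, so that it is not chosen on the results.

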#### Unsupervised group—physical activity recommendations

Participants will receive physical activity recommendations booklet (based on WHO guidelines) produced by ICESP. The booklet suggests different types of physical activity and exercise, such as aerobic, strength, and flexibility, outlines their benefits, and precautions participants should adopt while exercising. The booklet recommends exercise as part of a lifestyle behavioral change. Participants will be free to perform daily life activities and physical activity at home, at gyms or outdoors, with the aim of increasing overall physical activity including leisure time physical activity via structured exercise. A member of the research team will make telephone calls to the participants, which are scheduled to be done every 2 weeks, totalizing eight phone calls. In these calls, the researcher will apply a standardized follow-up questionnaire to monitor physical activity adherence.

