
#### Assessing physical activity every 2 weeks

Quantifying physical activity will be critical for indicating the level of adherence to the intervention and to assess whether the participants have moved towards adopting a more physically active lifestyle [86]. In addition to obtaining estimates of physical activity using accelerometry, a standardized questionnaire will be administered by a trained researcher in-person/face-to-face in the supervised canoeing group, and via telephone in the unsupervised group every 2 weeks. The periodic assessment and contact with the participants are also a key strategy to promote retention, especially in the home-based group. The questionnaire will be modified from the Brazilian version [87] of the Minnesota Questionnaire on Physical Activities, Sports and Leisure [88], which surveys time spent on various activities, both domestic and sports. This physical activity questionnaire will be used to measure 1) the time participants spent doing accumulated physical activities, including lifestyle physical activity and incidental movement, referred as “Unscheduled Movement”; 2) the time spent in physical activities specifically scheduled to meet the goal of 150 min of physical exercise per week; 3) and the total time spent sitting, whether in leisure activities (such as watching television and cell phones) or in work activities. Self-reported measures of physical activity and sedentary behavior have been criticized for low validity and reliability. As a result, caution is advised when relying on questionnaires to assess physical activity and sedentary behavior [89]. To address this issue, physical activity will also be assessed by accelerometer pre-intervention, at 8 weeks and post-intervention (16 weeks), aiming to provide a more objective estimate to compare and validate the follow-up physical activity and the sedentary behavior questionnaire.

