#### Physical activity level

Time, intensity, and frequency of physical activity engagement will be assessed using ActiGraph GT9X accelerometers (ActiGraph Pensacola, USA) at pre-intervention (with aims to provide baseline comparisons), during the intervention (mid-way, approximately 8 weeks of intervention), and post-intervention (after 16 weeks). The ActiGraph GT9X is a small, light-weight accelerometer (19 g; 4.6 cm × 3.3 cm × 1.5 cm) capable of recording accelerations in the vertical (Y), horizontal right-left (X), and horizontal front-back (Z) axes to compute vector magnitude [VM = √(axisY^2^ + axisX^2^ + axisZ^2^)]. The ActiGraph GT9X records accelerations over pre-defined time periods (“epochs”). Following which, Actilife software (ActiGraph Pensacola, USA) is used to convert raw acceleration data into “activity counts” for analysis. In this study, the GT9X+ will be initialized to record accelerations in 60-s epochs over a period of 7 days at each assessment time point. During this 7 days, participants will be asked to wear the GT9X attached to an adjustable elastic belt on their right hip in a vertical position [90, 91], and to remove the device only for sleeping and water-based activities (e.g., swimming, bathing).

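### One participant-random-factor model covers the eight-wave and three-wave activity outcomes; if correlation fades with time, its group-by-time F test runs at about 7–10% (eight waves) or 5–6% (three) instead of 5%

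*Protocol article*

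**What the plan says.** The Data analysis section sets a single model: linear mixed models having "group and time as fixed factors and participants as a random factor will be performed for each dependent variable". The variables listed there include "daily physical activity, and adherence to physical activity guidelines (assessed via accelerometry and questionnaire". Ordinal outcomes get the same treatment: "Ordinal data will also be analyzed using mixed models having group and time as fixed factors, and participants as random factor". On follow-up comparisons it says "Whenever a significant F-value is obtained, a post hoc test with" Tukey's adjustment will be carried out. The section names no residual covariance, sphericity correction or degrees-of-freedom method, and it does not name the group-by-time term.

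The outcomes under this one model have different numbers of waves:

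- **Activity questionnaire.** It is given in person in the supervised group "and via telephone in the unsupervised group every 2 weeks". The section on the unsupervised group counts the calls: "which are scheduled to be done every 2 weeks, totalizing eight phone calls".
- **Accelerometer.** It is worn at three times: before the intervention, "during the intervention (mid-way, approximately 8 weeks of intervention), and post-intervention (after 16 weeks").
- **Peak VO2 and most other outcomes.** They are measured twice, at baseline and after 16 weeks (Assessments section).

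**The concern.** A participant random factor alone is a random intercept. It makes the correlation between weeks 2 and 4 equal to that between weeks 2 and 16. With two occasions there is only one correlation, so nothing is lost. With eight, the assumption is strong.

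If neighbouring reports are more alike than distant ones, the model pools its within-person error over near and far pairs. That error is then too small for comparisons of distant waves and too large for neighbouring ones, and the F tests for time and group-by-time reject too often under the null.

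Better adherence to an active lifestyle opens the trial's hypothesis in the Study design section, and these repeated activity measures are the evidence for it. What is at stake is a somewhat raised chance of declaring that the arms' activity courses differ when they do not.

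**Working it through.** **Inputs from the protocol article.** Alpha 0.05 and 15 per group, raised by 20% to 18 (15 × 1.2 = 18), from the sample-size section; 8 questionnaire waves; 3 accelerometer waves; time as a factor; participant as the only random factor.

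**Assumed.** The correlation between waves. The only correlation in the article is 0.50, between pre-test and post-test in the VO2 sample-size calculation. The group-by-time term is also assumed, as the natural test of a difference in course.

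**Step 1: what the model implies.** With person variance σ_b² and residual variance σ_e², the correlation between any two waves is σ_b²/(σ_b² + σ_e²). With complete data the group-by-time test is the univariate repeated-measures F on (m − 1) and (2n − 2)(m − 1) degrees of freedom. For n = 18 that is 7 and 34 × 7 = 238 at eight waves, and 2 and 34 × 2 = 68 at three. For m = 2 the equal-correlation condition is met automatically.

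**Step 2: why the error term goes wrong.** Take AR(1) with r = 0.7 at eight waves. The average pairwise correlation is Σ(8 − k)·0.7^k / 28, for k = 1 to 7, = 11.337/28 = 0.405. The model bases the variance of every difference on 1 − 0.405 = 0.595. The true figures are 1 − 0.7^7 = 0.918 for first against last and 1 − 0.7 = 0.300 for neighbours. For first against last the standard error is too small by √(0.918/0.595) = 1.24.

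**Step 3: size of the planned F test.** Simulated null, 18 per arm, complete data, 20,000 trials per cell. ε is the sphericity index (1 means the F is exact).

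| True correlation | ε, 3 waves | F, 3 waves | ε, 8 waves | F, 8 waves |
|---|---|---|---|---|
| Equal, 0.5 | 1.00 | 4.9% | 1.00 | 5.0% |
| AR(1) 0.3 | 0.97 | 5.4% | 0.88 | 5.9% |
| AR(1) 0.5 | 0.92 | 5.3% | 0.72 | 7.5% |
| AR(1) 0.7 | 0.87 | 5.6% | 0.55 | 8.9% |
| AR(1) 0.9 | 0.82 | 6.0% | 0.40 | 10.6% |
| AR(1) 0.95 | 0.81 | 6.0% | 0.36 | 11.3% |
| Person effect 0.5 + AR(1) 0.5 | 0.92 | 5.3% | 0.72 | 6.9% |
| Person effect 0.3 + AR(1) 0.7 | 0.87 | 5.5% | 0.55 | 9.0% |
| Random slope, milder | 0.96 | 5.5% | 0.93 | 5.5% |
| Random slope, stronger | 0.90 | 5.5% | 0.81 | 6.2% |

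The first row reproduces the nominal 5%. Results with 15 per arm are much the same. Repeat runs at AR(1) 0.9 and eight waves gave 10.0 to 10.7%. The F for time is inflated to a similar degree (7.0%, 8.9% and 11.0% at AR(1) 0.5, 0.7 and 0.9).

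The correlations in the table are per wave. If the same process drives both instruments, 0.9 over two weeks becomes 0.9^4 = 0.66 over the eight weeks between accelerometer waves, which keeps the three-wave case at the mild end.

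**Step 4: post hoc comparisons.** When the first-to-last change difference is tested only after a significant F, it rejects at about 3 to 8% at eight waves and about 4 to 6% at three. Tukey-adjusted comparisons of the arms at the same wave reject in at most 1.5% of trials without the gate and 0.5% with it.

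**Step 5: after correction.** Over AR(1) 0.3 to 0.9, at 15 or 18 per arm, an unstructured covariance (computed as Hotelling's T² on the differences) gives 4.6 to 5.2% and Greenhouse-Geisser 3.8 to 4.9%. Comparing arms on each woman's mean over the eight reports gives 4.7 to 5.2% at 18 per arm in every scenario of Step 3.

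**The case against.** A reader might infer that tests on these outcomes run as high as 31%. The article does not support that. Rates near 30% arise only for a linear-trend difference at eight waves with strong serial correlation, and the plan enters time as a factor. Likewise, ungated and unadjusted first-to-last contrasts reach 6 to 19% at eight waves and 7 to 11% at three, but the plan tests pairs only after a significant F and with Tukey's adjustment. Under the global null, gated error cannot exceed that of the F.

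Three further objections carry weight:

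- The inflation depends on an assumed decay. Under equal correlation there is none. Decay is plausible for reports 2 against 14 weeks apart, but it is not documented.
- Naming participants as a random factor does not exclude a residual covariance structure, and an analysis plan that is not shown may specify one. Still, the article does state the within-person structure, and states it for every outcome. The point is therefore about a stated choice, and silence alone is not the complaint.
- Peak VO2 and the other two-wave outcomes are untouched.

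In the other direction, the gate is not complete protection. The post hoc sentence does not say which F must be significant, and both arms receive the activity advice, so a shared time effect could open it. Tukey comparisons across times within one arm then ran at 5.6 to 7.5% at eight waves, against 5.1% under equal correlation.

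**Conclusion.** The point holds in a limited form. Read as written, the model imposes equal correlation on outcomes with eight and three waves. If correlation decays (AR(1) 0.5 to 0.9, with or without a stable person effect), the group-by-time F runs at about 7 to 10% at eight waves. Over a wider set of assumptions it runs at about 6 to 11%, and close to nominal under a mild random slope. At three waves it is about 5 to 6%, which is of little practical consequence.

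These figures assume complete data, 18 per arm and no true difference in course. They apply to secondary outcomes only. Priority is low: worth correcting because the remedy is cheap, with no bearing on the primary analysis.

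**What to change.** Amend the Data analysis section as follows.

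- **Questionnaire, eight waves.** Either apply a Greenhouse-Geisser-type degrees-of-freedom correction, or a covariance that allows unequal correlations, to the time and group-by-time tests; or make the between-arm comparison of each woman's mean over her available reports the main test. The Discussion says that most women in the pilot's unsupervised group did not answer the calls, so the chosen method must work with missing reports. The classical correction is built for complete data; the other two options cope more readily.
- **Accelerometer, three waves.** Use an unstructured covariance with Kenward-Roger degrees of freedom.
- **Outcomes measured only before and after.** Keep the participant random factor.
- **Group-by-time term.** Name it, and say which significant F opens the post hoc comparisons.

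The cost is wording, slightly lower power for tests of time course, and a few more covariance parameters: 3 × 4 / 2 = 6 for the accelerometer instead of 2. A fully unstructured matrix at eight waves would need 8 × 9 / 2 = 36 parameters from 36 women, so a simpler structure, the correction or the mean is the more practical choice there. If the mean becomes the main test, the course over the eight reports can still be described or tested secondarily with a corrected F. No new data and no change in sample size are needed.
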